## Methods and Design

### Overview

This study uses a two-group (experimental vs. attention control), double blind randomized controlled design with three measurement points including pre-treatment baseline, 3-month (end of treatment) and 12-month follow-up. The target population is smoking mothers enrolled in Philadelphia, Pennsylvania’s WIC program – a community-based health system that serves over 70,000 low-income families annually. The primary outcome is bioverified child TSE and the secondary outcome is bioverified maternal smoking abstinence. The study design is guided by CONSORT criteria [27] and is approved by Temple University’s Institutional Review Board (protocol number 23188). In the clinics, WIC nutrition counselors will be trained to implement the Ask, Advise, Refer (AAR) [23] intervention for addressing child TSE and parental smoking. All smokers, including those who do not wish to be referred to the BLiSS trial, will receive the state quitline number, which also helps them to access NRT. Eligible consented mothers will complete baseline assessment and get randomized to receive one of the two interventions: (a) the multimodal behavioral intervention (AAR + MBI) which will include telephone-based quitline counseling that focuses on reducing child TSE and maternal smoking cessation, an integrated mobile app linked to a web-enabled counselor portal to facilitate self-monitoring, text messages and educational video clips related to smoking, and NRT; or (b) the attention control (AAR + Control) intervention that includes similar contact time AAR + MBI with telephone-based nutrition education, separate mobile app and text-message delivered educational video clips that focus on improving family nutrition.

### Participants

The trial’s sample will be recruited in partnering WIC clinics. WIC mothers who have received the WIC clinic AAR intervention and are referred to the trial will be eligible if they are English-speaking, at least 18 years old, report smoking, own a smartphone, and report that their child under the age of 6-years old is exposed to tobacco smoke in their home. For mothers with multiple children under the age of 6, we will select the youngest child not in diapers or the oldest in diapers if all children are still in diapers. Exclusion criteria include pregnancy and presenting issues that can interfere with the ability to provide informed consent or follow study procedures, such as psychosis, inadequate health literacy, or (non-nicotine) drug dependence. Figure 1 shows participant flow through clinic intervention, enrollment, intervention, and data collection.

**Fig. 1 Fig1:**
[figure not shown]
Flowchart of trial recruitment, assessment and intervention

### Procedures

Prior to initiating participant recruitment, we will conduct a formative analysis of current tobacco intervention practices among professional and paraprofessional staff who work in Philadelphia WIC clinics. This preliminary research will facilitate the translation and implementation of AAR best practices into routine WIC clinic operations and client flow that will minimize both staff and participant burden. We will then provide group training among all staff that highlights the child TSE problem and its consequences, challenges maternal smokers have in quitting smoking, and the pivotal contributing role of community health workers in tobacco control efforts. In addition, WIC nutrition counselors will receive more intensive training in the specific steps to implementing the Ask, Advice, Refer intervention.

After WIC staff refer smoking mothers with exposed children to the trial, trained research assistants will consent eligible participants and collect self-report data at baseline. Data will be collected via structured computer assisted telephone interviewing. This method reduces literacy barriers, minimizes participant burden, and maximizes data reliability. After baseline, participants are randomized to condition. A permuted blocks design was used to randomize participants stratified by clinic site and presence of other smokers in the home living with the participant (yes/no). The randomization schedule was seeded using values obtained from random.org and the project biostatistician provided the allocations to the data collection team in sealed opaque security envelopes. To preserve condition masking, participants will be randomized after baseline data collection and immediately prior to a treatment orientation home visit. During the orientation home visit, participants receive a binder with intervention materials that are relevant to their assigned intervention condition. Research staff also download a mobile app specific to condition on participants’ smartphones and show an app video tutorial, the link to which is left with the participant. The child’s urine cotinine sample is also collected during the home visit.

Research staff blind to treatment assignment will conduct 3-month end-of-treatment and 12-month follow-up via structured telephone interviews. After each telephone assessment, another home visit is scheduled to obtain child urine cotinine samples and participant saliva to bioverify child TSE level and participant smoking status, respectively. In addition to a saliva sample, participants provide an expired CO sample given the potential that participants may be using NRT. Various procedures are used to reduce attrition, including reminder postcards and text messages, flexible scheduling, and financial retention incentives for completing assessments.

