### Aims and hypotheses

Aim 1: Test the hypothesis that a program integrating a WIC system-level “AAR” intervention with an intensive multimodal behavioral intervention (AAR + MBI) will be more effective in reducing child TSE (primary outcome) than a WIC system AAR plus an attention control intervention (AAR + Control). *Hypothesis 1:* Compared with AAR + Control children, those in the AAR + MBI condition will have significantly greater reductions in parent-reported daily TSE and child urine cotinine from baseline to 3- and 12-month follow-up.

Aim 2: Test the hypothesis that the multilevel AAR + MBI will be more effective at increasing maternal quit rates (secondary outcome) than AAR + Control. *Hypothesis 2:* Compared with the control group, mothers in AAR + MBI will have a significantly greater bioverified, 7-day point prevalence quit rate at 3- and 12-month follow-up.

Aim 3: Test hypotheses that changes in theoretically important variables will mediate the effects of AAR + MBI on child TSE and parent smoking outcomes. *Hypothesis 3*: Compared with parents in the AAR + Control condition, parents in the AAR + MBI condition will evidence greater increases in TSE protective behaviors, social support, urge management coping skills, and self-efficacy related to protecting child from TSE and quitting smoking from baseline to 3-month follow-up. In turn, these changes in mediator variables will account for between-group differences in TSE and cessation outcomes at month 12 (e.g., change in child cotinine from baseline to 12-month follow-up).

Aim 4: Explore factors that may influence outcomes and moderate intervention effects, including presence of other smokers at home, nicotine dependence, depressive symptoms, weight concerns, and intervention dosage as measured by quitline, NRT, and app usage.

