#### Covariates and moderators

Four variables will be assessed as potential control variables and moderators of intervention effects: (a) Nicotine dependence will be measured with the reliable and validated Fagerström Test for Cigarette Dependence [43]. (b) Depressive symptoms will be measured with the Center for Epidemiological Studies Depression Scale, which are validated, reliable and useful in smoking studies [44]. (c) Weight concerns will be measured using a 6-item validated scale that measures general and smoking-specific weight concerns [45]. (d) Other smokers in mothers’ homes will be assessed using a standard, content valid item. Additional demographic and smoking history variables will be measured and assessed for possible association with outcomes.

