### Analytic plan

The predictor is intervention group (AAR + MBI vs. AAR + Control) and the two endpoints include child exposure (continuous primary outcome) and parent cessation (dichotomous secondary outcome). Primary analyses will use an intention-to-treat approach and missing data will be addressed using multiple imputation. In sensitivity analyses, we will perform complete case analyses and investigate the impact of data that is potentially missing not at random. We will compare child cotinine change scores between intervention arms using multilevel random-effects linear regressions in which we include randomization arm as a fixed effect and WIC clinic as a random intercept to account for potential clustering within clinic. Potential confounders (e.g., nicotine dependence) will be added as covariates as necessary. We will use multiple logistic regressions with random intercepts for clinic to compare bioverified self-reported quit status (yes/no) between randomization arms at 3 and 12 months. To investigate mediation pathways, we will use a structural equation approach with change in cotinine levels and parent quit status as the outcomes. We will ensure that the intervention is associated with the potential mediators (e.g., self-efficacy) and that the mediators are associated with the outcomes. We will also use cluster-adjusted bootstrap standard errors for assessment of the mediated effect in which the variables are measured in a temporal ordering consistent with a causal pathway. For moderation analyses, we will use random-effects multiple regression modeling the change in cotinine levels and parent quit status, using confounding variables as necessary.

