#### Power analysis

We chose our sample size so that we would have at least 85% power to detect between-group differences in the primary outcomes (3- and 12-month child cotinine). Using an estimate of 20% 1-year follow-up attrition based on the KiSS trial, we expect to have 298 participants at 12 months (372*80% retention = 298, or 149 per group). With 149 participants per group, we will have 85.7% power to detect an effect of 0.23 in the log cotinine change scores between randomization arms.

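### Other smokers in the home is a randomisation stratum but not a required term in either outcome model; leaving it out would cost a little efficiency, and requiring it is nearly free

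*Protocol article*

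**What the plan says.** **Allocation.** The Procedures section of the protocol article names two stratification factors: "A permuted blocks design was used to randomize participants stratified by clinic site and presence of other smokers in the home". The second is recorded as yes or no.

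**Cotinine model.** The Analytic plan commits to a multilevel linear regression of cotinine change scores in which "we include randomization arm as a fixed effect and WIC clinic as a random intercept to account for potential clustering within clinic". Further terms follow a general rule: "Potential confounders (e.g., nicotine dependence) will be added as covariates as necessary".

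**Quit model.** The same section states: "We will use multiple logistic regressions with random intercepts for clinic to compare bioverified self-reported quit status (yes/no) between randomization arms". No covariate is named for it.

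**Status of the second stratum.** Under Covariates and moderators, other smokers in the home is one of a group introduced by "Four variables will be assessed as potential control variables and moderators of intervention effects". Aim 4 sets out to "Explore factors that may influence outcomes and moderate intervention effects, including presence of other smokers at home".

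One stratum is therefore fixed in both models. The other may be added but need not be.

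**The concern.** The usual principle is that the analysis reflects the randomisation. Stratified blocks remove most of the chance difference between arms in the stratifying factor, so the treatment contrast varies less than under simple randomisation. A linear model without the factor does not know this: its residual variance still contains the variation that the factor explains, so its standard error overstates the real variability of the contrast. Intervals are then too wide and the test rejects less often than its nominal level.

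The covariate rule fits this variable poorly. It speaks of confounders, and a factor balanced by stratified blocks is not expected to differ between arms. The rule also gives no criterion, so the content of the primary model could be settled after the data are seen. At stake are some precision in the primary cotinine comparison, a smaller amount of power in the quit comparison, and one avoidable discretionary choice.

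**Working it through.** **Inputs from the document.** 372 mothers randomised and 20% attrition: 372 × 0.80 = 297.6, or 298, which is 149 per group. The Power analysis section states: "With 149 participants per group, we will have 85.7% power to detect an effect of 0.23 in the log cotinine change scores".

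**Assumptions, because the article gives no value.** Two-sided alpha of 0.05; R², the share of variance in log cotinine change explained by other smokers in the home; equal variances; exact balance on the stratum in the analysed set.

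**The plan's own power figure.** If 0.23 is a standardised difference (SD 1), power with 149 per group is 51.0% two-sided or 63.3% one-sided, so 85.7% is not reached. It can be matched only by solving for an SD that is not stated:

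- SD = 0.23 / [(1.960 + 1.067) × √(2/149)] = 0.23 / (3.027 × 0.1159) = 0.656, two-sided.
- The one-sided equivalent is 0.732.

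The rest uses 0.656 as the total SD, so the effect divided by its nominal standard error is 3.027.

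**Cotinine model, formulas.** With balance on the stratum, the true standard error of the contrast is √(1 − R²) times the one that the model without the stratum reports.

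- Standard error ratio, reported to true: 1/√(1 − R²)
- Actual type I error without the term: 2 × [1 − Φ(1.96/√(1 − R²))]
- Power without the term: Φ((3.027 − 1.96)/√(1 − R²)) = Φ(1.067/√(1 − R²))
- Power with the term: Φ(3.027/√(1 − R²) − 1.96)

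| Assumed R² | SE ratio | Actual alpha, term omitted | Power, omitted | Power, included | Difference (points) |
|---|---|---|---|---|---|
| 1% | 1.005 | 4.9% | 85.8% | 86.0% | 0.2 |
| 5% | 1.026 | 4.4% | 86.3% | 87.4% | 1.1 |
| 10% | 1.054 | 3.9% | 87.0% | 89.1% | 2.1 |
| 20% | 1.118 | 2.8% | 88.4% | 92.3% | 3.9 |

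Worked line for R² = 10%: √0.90 = 0.9487. Omitted: Φ(1.067/0.9487) = Φ(1.125) = 87.0%. Included: Φ(3.027/0.9487 − 1.96) = Φ(1.231) = 89.1%.

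The right comparator is the omitted-term power in the same row, not 85.7%. Stratified allocation already makes the contrast less variable, so the model without the term gains a little as well.

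**Simulation check.** 298 participants, 10 clinics, blocks of 4 within clinic by stratum (clinic number and block size assumed), no clinic effect, 6,000 runs per setting.

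| Assumed R² | Alpha, omitted | Alpha, included | Power, omitted | Power, included |
|---|---|---|---|---|
| 1% | 4.9% | 4.9% | 85.8% | 86.0% |
| 5% | 4.2% | 4.8% | 85.6% | 86.6% |
| 10% | 3.4% | 4.6% | 87.1% | 89.1% |

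These agree with the formulas to within about two simulation standard errors.

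**Quit model.** The linear formula does not carry over, so this was simulated: 372 participants, a 10% quit rate among control mothers without other smokers in the home, a treatment odds ratio of 2.5, an odds ratio for other smokers of 0.5 or 0.25, and 8,000 runs. All these values are assumed, and no clinic effect was included.

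| OR, other smokers | Mean log OR, omitted / included | Mean reported SE, omitted / included | Power, omitted / included |
|---|---|---|---|
| 0.5 | 0.930 / 0.943 | 0.346 / 0.348 | 78.9% / 79.3% |
| 0.25 | 0.914 / 0.947 | 0.378 / 0.384 | 69.8% / 71.4% |

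Adding the stratum slightly raises the reported standard error. Without the stratum, the reported standard error does not exceed the observed spread of the estimates (0.346 against 0.354, and 0.378 against 0.382), so it is not too wide. The loss of 0.4 or 1.6 points comes from the unadjusted log odds ratio lying closer to zero.

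**The case against.** The best reply is that nothing is excluded. The article lists other smokers in the home as a possible control variable, allows covariates in the cotinine model, and calls the quit model a multiple regression. A final covariate list usually belongs in a statistical analysis plan, which is not shown. This limits the point but does not remove it. The article does state its models, gives one stratum a fixed place, and leaves the other to a rule without a criterion. Improving a model that has been stated is different from asking for a missing detail.

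A reader might go further and infer that standard errors will be too wide and power lost in both models. The document does not support that, for these reasons:

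- The effect needs the stratum to be omitted, and the article does not say that it will be. Nor does it state a selection rule based on imbalance. For additional demographic and smoking-history variables it describes assessment of association with outcomes; a similar screen here would tend to keep a strongly prognostic stratum.
- The effect needs the stratum to predict change in cotinine. A stable household feature may predict the level of exposure well and the change much less. The article offers no estimate, and nothing in it supports the upper end of the R² range.
- The article gives no reason for choosing this stratum. Aim 4 says only that it may influence outcomes.
- Measuring the gain from 85.7% would overstate it: at R² of 5, 10 and 20% it would suggest 1.7, 3.4 and 6.6 points instead of 1.1, 2.1 and 3.9.
- A standard error that is too wide describes the linear model, not the logistic one.

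It also stands that the error is on the safe side: omission does not bias the cotinine contrast or raise its false-positive rate.

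**Conclusion.** The point holds in a limited form. A factor used to stratify the randomisation, which the protocol article itself says may influence outcomes, is not a required term in either outcome model.

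The consequence is conditional and modest. If the stratum is omitted and explains 1 to 10% of the variance in cotinine change, the cotinine test runs at 4.9 to 3.9% instead of 5% and gives up 0.2 to 2.1 points of power. At 20% these become 2.8% and 3.9 points. Planned power is not undercut, provided the implied SD of 0.656 is the total SD. For quit status the loss is 0.4 to 1.6 points in the settings simulated, through attenuation of the odds ratio.

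The R² values, SD, alpha, quit rate, odds ratios, number of clinics and block size are all assumptions. The document allows the direction to be stated for the cotinine model, but not the actual size. The case for acting rests on how little the change costs and on removing a discretionary choice from the primary model, not on a large loss.

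**What to change.** State that the cotinine and quit-status models at 3 and 12 months include other smokers in the home (yes/no, with the value used at randomisation) as a fixed effect, next to the planned random intercept for clinic, regardless of observed balance. Keep the discretionary covariate rule, if it is kept at all, for variables that are not randomisation strata.

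The cost is one sentence of analysis text and one degree of freedom per model. The value had to be known to allocate each participant, so no new data are needed, and the sample size does not change.

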### Interventions

#### WIC system intervention (both groups)

Specific procedures for delivering the WIC system intervention includes the following steps: At each clinic visit, mothers complete a 3-item smoking and TSE survey included in their pre-appointment paperwork. A nutrition counselor reviews the survey and offers all mothers with exposed children advice about dangers of TSE and benefits of reducing exposure. Mothers also receive a pamphlet reiterating counselors’ TSE health messaging (e.g., “There is no safe level of TSE; ask your WIC counselor about the BLiSS program and other smoking treatment services”). Nutrition counselors discuss the BLiSS program and mark on the survey whether smoking mothers want a referral to the trial. Project staff proactively call these mothers for eligibility screening.

We facilitate assimilation of the protocol into routine WIC clinic work flow through adoption, implementation, and maintenance phases. During the adoption phase, research staff will provide system-wide training for all professional and paraprofessional WIC staff about maternal smoking and child TSE. This training also highlights the relevance of creating a pro-TSE-reduction culture and social norms within the WIC organization and how such norms may impact tobacco control efforts in the community. During implementation, project staff will meet with WIC counselors at each clinic sequentially to discuss the BLiSS program in the context of improving the quality of WIC clients’ care. WIC counselor input guides procedures that embed the AAR protocol in existing workflow to minimize staff and client burden. BLiSS staff will model and role play execution of the AAR protocol and troubleshoot barriers to AAR delivery to maximize adherence. Similar to our previous trial [20], implementation also involves academic detailing, which includes hanging posters and placing pamphlets in WIC clinics that reflect norms supporting child TSE reduction efforts, provide consistent health messaging across multiple modes of intervention, and prompt nutrition counselors to advise and refer smoking mothers to the trial. During the maintenance phase, project staff will provide AAR fidelity monitoring reports to the WIC management team and nutrition counselors that include number of referrals received and referred mothers’ reports about the TSE advice and written materials they received at WIC.

### Attention control intervention: nutrition education (AAR + Control)

Trained health counselors deliver the Control intervention. Training, in-home intervention orientation, and multimodal behavioral intervention procedures parallel procedures described in the MBI arm below. However, the content of the Control behavioral intervention centers on improving nutrition on a budget, with an emphasis on reducing sugar intake and increasing fruit and vegetable consumption. The purpose of the Control group is to provide equivalent attention and contact between the two conditions while providing distinctly different behavioral intervention content. At the orientation, BLiSS staff offers participants the state quitline number including information that the quitline delivers free NRT. Staff also provide the written tool kit developed by Sesame Street Workshop, *Food for Thoughts: Eating Well on a Budget* [28], that includes nutrition guidelines, recipe cards, and colorful books with activity suggestions as well as videos about nutrition on a budget and fruit and vegetable consumption. Additionally, staff use food models to demonstrate recommended serving sizes and download the Fooducate mobile app (with video tutorial) to participant smartphones. This app scans barcodes on foods to provide real time nutrition information. Staff also provide participants with the number of the state quitline and are informed they can receive smoking cessation counseling and free NRT by calling the number. Finally, during the weeks between the orientation and 3-month end-of-treatment phone assessment, participants will receive up to 5 telephone nutrition education calls, 10 nutrition education video clips via text messaging, and inter-session text message follow-ups and appointment reminders.

